## Discussion

This paper describes the study protocol for a quasi-experiment of an extended maintenance intervention, which aims to maintain positive benefits of an initial 10-week stay at a residential health camp on children's life satisfaction and BMI after they have returned to their homes. Both the initial intervention at the health camp, the standard maintenance intervention (control group) and the extended maintenance intervention are developed by practitioners and delivered for other purposes than research.

Center for Intervention Research, at The National Institute of Public Health, SDU in Denmark was commissioned by the Liljeborg Foundation and the DCSH to conduct an external research-based evaluation of the implementation and effectiveness of the intervention. It is however challenging to evaluate real world practice in a rigorous research design.

The practical set-up of the health camps and the maintenance interventions limited our methodological opportunities and forced us to make some compromises to the ideal research design. We would have preferred to conduct a RCT study, but it will not be possible to randomize children into intervention and control groups as the DSCH controls the allocation procedure. Instead we will approach the evaluation as a quasi-experiment with the risk of selection bias (30). We do not expect large systematic differences between the two groups as the DSCH's allocation procedure is motivated by which municipality the child comes from and both intervention and control groups recruit children from municipalities with a different socioeconomic range. However, we will assess baseline equivalence between the two samples using descriptive statistics on key variables and we will adjust the effect analyses for key covariates chosen a priori. The study is also limited by the self-reported height and weight measures at 3 months and 1 year follow up (45, 46). However, we hypothesize that a potential disagreement between objective measures and self-reported measures will be similar in both intervention and control groups. The objective and self-reported measures at baseline and post camp will enable us to explore this hypothesis.

The strengths of this study include the use of external evaluators, the systematic approach to evaluation planning, the research-based evaluation design, the prospective trial registration, and the development of a program theory to structure the evaluation.

There was no explicit program theory for the extended maintenance intervention when we entered the study. We developed a program theory together with intervention providers to structure the evaluation and prevent ‘black box' evaluation (32). As external evaluators it was highly important that we spent time on getting to know the organization and on reaching a common understanding of the purpose and working mechanism of the intervention with intervention providers (47). During the development of the program theory, it became apparent how each of the intervention coordinators and the principal had their own tacit assumptions about the purpose and working mechanism of the intervention. Thus, the workshop on program theory also benefitted the organization as they were made aware of their different views on working mechanism (48).

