#### Referral to Health Camp and Characteristics of Children

Any child and their family can apply for a stay at a DCSH health camp, and it is free of charge since DCSH raises money to run the camps. In the application form, the child, family, or other relevant people describe the rationale for why a stay at a health camp is thought to be a good idea for the child including the concerns and challenges the child faces. The application must be supported by the school and the child's family physician along with a social worker or a psychologist if applicable. The application is sent to DCSH, who distribute the applications to the principal at one of the five camps. The principal assesses the application and considers whether the child would benefit from a stay. Overall, children are accepted unless they do not fulfill the age group specifications, have severe medical symptoms (either psychiatric or physical) or are considered in need of a placement with more support than what can be offered at the camps e.g., for maladjusted children. The camp program is considered a pedagogical offer, not a psychiatric one. If the principal has any uncertainties of whether the child has medical issues, the application is sent to a pediatrician affiliated with DCSH. The pediatrician considers if the applicant could benefit from a stay based on the medical issues. E.g., children are accepted if they are diagnosed with only mild symptoms of a psychiatric disease e.g., ADHD. The principal can also arrange for an early meeting with the child and family to disclose whether the child is believed to benefit from a stay.

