#### Sampling and Allocation to Intervention Groups

Half of the children from the Liljeborg health camp is offered the extended maintenance intervention. The allocation to the intervention group is done by a secretary at the DCSH. The allocation is not random but based on the home municipality of the child (geographical criteria). The Liljeborg health camp covers both municipalities in the Capital Region of Denmark and the Region of Zealand and the distribution is ~50/50 from each region. All 10 municipalities in the Region of Zealand covered by the Liljeborg health camp are allocated to the intervention group. The control group includes children from the Liljeborg health camp along with the four other health camps receiving the standard maintenance intervention (control group 1) and children from the Liljeborg health camp allocated to the standard maintenance intervention (control group 2).

Blinding is not possible in this setting, and the standard maintenance intervention families at Liljeborg will have an idea of the activities going on in the extended maintenance intervention. For the four remaining health camps, families are not aware of any other type of maintenance interventions than the one offered at that specific home, which is the standard maintenance intervention.

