#### Intervention Group: Extended Maintenance Intervention

The extended maintenance intervention is also delivered by an intervention coordinator who is assigned to a family. Some activities are identical to the standard maintenance intervention such as family day and follow up day along with phone calls (Table 1). The extended maintenance intervention encompasses several new initiatives compared to the standard maintenance intervention. It has a duration of ~16 weeks, 6 weeks while the child is at camp and 10 weeks afterwards. The intervention coordinator will participate in home visits and can also participate in different activities such as school visits and network meetings and assist the family in initiating new sports activities or other relevant activities (Table 2). The number of each of the activities are decided in corporation between the family and the intervention coordinator. The intervention has been in constant development since the beginning of 2018 and it is an ongoing process.

**Table 1 T1:** Main similarities and differences between the two maintenance interventions.

**Family collaboration**	**Standard maintenance intervention (control group)**	**Extended maintenance intervention (intervention group)**
Intervention provider	Intervention coordinator	Intervention coordinator
Duration	9 weeks	16 weeks
Intervention concept	Standard	Tailored to each child
Information day before camp	X	X
Family day during camp	X	X
Follow up day 4 weeks after camp	X	X
Phone call/texts to follow up	X	X
Home visits during and after health camp		X
Network meetings		X
School meetings		X
Meeting with health worker or social worker in home municipality		X
Start-up of sports activities		X

**Table 2 T2:** Activities in the extended maintenance intervention and frequency.

**Activities**	**Number**
**Home visits:** The intervention coordinator visits the child's home and talks to the parents and the child, most often separately. The first visit is while the child is still at camp and therefore solely involves a talk with the parents	2–5
**Network meetings:** The intervention coordinator arranges a meeting with relevant participants e.g., parents, schoolteacher, school principal, social and/or health worker from the municipality etc.	0–2
**School meeting:** The intervention coordinator visits the schools along with the child to tell the classmates about the child's experiences at the camp	0–1

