#### Developing a Program Theory of the Extended Maintenance Evaluation

The extended maintenance intervention is developed by the DCSH. It is based partly on recommendations from the previously mentioned evaluation from 2016 (27), recommending an extended collaboration with stakeholders in the home environment. However, the ideas for its content grew along the way and the actual development was done in collaboration between the principal and the intervention coordinators at Liljeborg health camp as an ongoing process. It is based on practical experiences, and with a focus on the narrative approach of changing the child's story telling about themselves to a more positive one as mentioned above. The ideas and assumptions behind the intervention were written down by one of the intervention coordinators during the development process, but in very general terms and there existed no explicit program theory when the research group entered the project. Thus, in order to plan a thorough process and effect evaluation design and avoid a black box evaluation we aimed to identify the exact content of the intervention and elicit the assumed but tacit working mechanisms of the intervention (32).

We started out by reviewing internal documents at the Liljeborg health camp concerning all five health camps. It consisted mainly of working manuals describing everyday life at the health camps, the activities and daily structure at the camps, the collaboration with families and the pedagogical philosophy determining the theoretical approach to the children as mentioned above. The documents also contained a description of the intervention content of the extended maintenance intervention at Liljeborg health camp, the allocation strategy of the maintenance intervention and a description of the self-invented ‘life satisfaction compass'.

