### Data Analysis

We will use descriptive statistics to investigate baseline equivalence and loss to follow up. We will graphically visualize the development over time in both intervention group and control group 1 for the primary and secondary outcomes.

We will analyze the effectiveness of the extended maintenance intervention compared to control group 1 on the primary and secondary outcomes, using linear regression analysis and on explorative outcomes using logistic regression analyses. We will apply an intention-to-treat approach including all children in the intervention group they initially have been allocated to irrespective of whether they have completed the intervention or are lost to follow-up. Missing data will be replaced by multiple imputation. We will perform complete case analysis for sensitivity analyses.

The effect analyses will be adjusted for baseline factors including gender and age of the child, life satisfaction, BMI-*Z* score, and parental socioeconomic position.

For the total population at all five camps, we will calculate the standard deviation of the primary and secondary outcomes right after camp to calculate Cohen's *d* effect size.

Furthermore, we will perform sensitivity analysis restricted to the data from the Liljeborg health camp to identify any differences between camps (control group 2). We will investigate the association between intervention dose and effect (per protocol analyzes).

We will investigate if the effect differs by subgroups (see moderators in Figure 2).

We will summarize process measures using appropriate descriptive statistics including proportions, means (SD), and medians (IQR).

We will identify who is in most need of the intervention and find out who does not need the intervention.

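### Allocation by home municipality is given as grounds for comparable groups, but at Liljeborg it makes the arm foreseeable at acceptance, and apart from the baseline ladder no named covariate measures the problems on which intake may act

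*Protocol article*

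**What the plan says.** The relevant statements are spread over several sections of the protocol article.

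- **Allocation** (Sampling and Allocation to Intervention Groups): "The allocation is not random but based on the home municipality of the child". All 10 Region of Zealand municipalities served by Liljeborg receive the extended intervention. Other Liljeborg children, and every child at the other four camps, receive the standard one. There is no blinding.
- **Intake** (Referral to Health Camp and Characteristics of Children): DCSH sends each application to one camp, and then "The principal assesses the application and considers whether the child would benefit from a stay". Acceptance is the default, with exceptions for age, severe medical symptoms, or a need for more support than a camp can give. Inclusion covers children signed up for a stay, so enrolment follows this decision.
- **The Liljeborg principal** (Developing a Program Theory): for the extended programme, "the actual development was done in collaboration between the principal and the intervention coordinators at Liljeborg health camp". Qualitative Data Collection describes the principal as central to developing and refining it.
- **Comparability** (Discussion): after conceding a risk of selection bias, the article states "We do not expect large systematic differences between the two groups". It gives two reasons: allocation follows municipality, and both groups recruit from municipalities of differing socioeconomic standing.
- **Safeguards** (Data Analysis): "We will use descriptive statistics to investigate baseline equivalence and loss to follow up". The effect models adjust for baseline factors including gender, age, life satisfaction, BMI-Z and parental socioeconomic position. A sensitivity analysis is restricted to Liljeborg.

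**The concern.** A rule fixed by geography before any child applies gives no concealment. Anyone who knows the rule and sees the address knows the arm. If a judgement about suitability is made at that point, the children accepted can differ between arms even when the underlying populations are alike. This is the identification problem familiar from cluster-allocated trials. The socioeconomic argument concerns the municipalities, not which children from them are accepted.

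A difference of this kind would enter the primary estimate as if it were an intervention effect, or would mask a real one. The traits most likely to matter are the severity of social and mental problems, because one ground for refusal is needing more support than a camp can offer. The named adjustment set reaches these only through the baseline ladder score.

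**Working it through.** **1. Is the arm foreseeable, and to whom?** Set the sections side by side:

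| Step | Who decides | Can the arm be foreseen? |
|---|---|---|
| Support for the application | School, family physician, others if relevant | Nothing says they know of the extended offer |
| Distribution to a camp | DCSH | Possibly; no rule for distribution is stated |
| Acceptance at Liljeborg | Principal, co-developer of the programme | Yes, from the home municipality |
| Acceptance at the other four camps | Their principals | Every child is a control, so no choice between arms |

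The firm link is acceptance at Liljeborg. It governs all of the roughly 144 intervention children and 144 of the 894 controls; the other 894 − 144 = 750 controls come from camps with a single arm.

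**2. What do the planned safeguards reach?**

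- The baseline comparison can show imbalance in measured traits of enrolled children. It cannot show whether refusal differed.
- The Liljeborg-only analysis compares children accepted by the same principal, so between-camp differences in intake drop out. Within Liljeborg, municipality still fixes the arm, so selection by municipality remains.
- WHO-5 and the school-bullying item are listed in Table 3 for all children at baseline, but neither is among the named covariates.

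**3. The plan's own scale.** Inputs from Sample Size Calculations: SD 2.1, groups of 144 and 894, power 80%. Alpha is not stated; two-sided 0.05 is assumed because it reproduces the figures.

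- SE = 2.1 × √(1/144 + 1/894) = 0.1886
- Detectable difference = 0.1886 × (1.960 + 0.842) = 0.528, stated as 0.53
- For 132 and 822: SE = 0.1969, detectable difference 0.552, stated as 0.55

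Both figures reproduce.

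**4. Effect of an assumed residual difference.** The documents give no figure for intake selection. As an illustration, suppose the share of children with serious social or mental problems differs by 10 to 20 percentage points between arms, and that these children score 0.5 to 1.0 ladder points lower at 1 year after adjustment for the named covariates.

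- Bias b = 0.10 × 0.5 = 0.05 to 0.20 × 1.0 = 0.20 points
- As a share of the detectable difference: 0.05/0.53 = 9% to 0.20/0.53 = 38%
- In standard errors: 0.05/0.1886 = 0.27 to 0.20/0.1886 = 1.06
- False-positive rate = Φ(b/SE − 1.96) + Φ(−b/SE − 1.96) = 5.8% to 18.5%

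With 132 and 822 children, b = 0.20 gives 17.4%.

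If the bias runs against the intervention and the true effect is 0.53, power falls from 80% to Φ(0.48/0.1886 − 1.96) = 72% at b = 0.05, and to Φ(0.33/0.1886 − 1.96) = 42% at b = 0.20.

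**The case against.** The strongest reply is that the article is open about this. It calls the design a quasi-experiment at risk of selection bias, hedges its expectation to large differences, gives a second reason, and plans a baseline check, adjustment and a same-camp sensitivity analysis. Acceptance is the default, and a pediatrician is consulted when medical issues are in doubt. Baseline life satisfaction, already a covariate, is the outcome itself and will absorb part of any imbalance. The covariate list is introduced as non-exhaustive. All of this stands. It narrows the point without removing it, because municipality allocation is still offered as a reason for comparability.

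Three stronger readings are tempting, and the documents do not support them:

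- **That referrers select by arm.** The article says of each application that "The application must be supported by the school", and of the extended programme that "The intervention has been in constant development since the beginning of 2018". Coordinators do deal with schools and municipal staff. A reader might infer that schools in intervention municipalities refer with the extended offer in mind. But those contacts concern children already in the programme, and nothing says that referrers know of the offer.
- **That nothing in the plan could reveal the problem.** Selection biases the result by changing who is enrolled. A baseline comparison of enrolled children addresses that for measured traits, though not for refusals.
- **That selection took place.** No refusal counts are given, and nothing in the article suggests that any principal chose by arm.

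**Conclusion.** The concern holds in a limited form. Municipality allocation is not grounds for expecting comparable groups: at Liljeborg it makes the arm foreseeable when a person involved in the programme's development assesses the application. The room for discretion is restricted but real. The planned safeguards cover part of the risk and leave selection by municipality within Liljeborg.

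The size is unknown. A false-positive rate of 5.8% to 18.5% follows only if a difference of 0.05 to 0.20 points survives adjustment. The lower end is negligible and the upper end is not. The calculation uses the plan's unadjusted SD and full group sizes, assumes two-sided 0.05, and takes no view on the direction of bias. The change is worth making because it costs almost nothing, not because bias has been shown.

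**What to change.** 1. Qualify the sentence in the Discussion so that allocation by municipality is no longer given as a reason to expect comparable groups. State that at Liljeborg the arm could be foreseen at acceptance.
2. Add baseline WHO-5 and the baseline school-bullying item to the adjustment set, in both the primary analysis and the Liljeborg-only analysis.
3. Include both in the baseline-equivalence table, with separate columns for extended, Liljeborg standard and the four other camps.
4. Optional, if DCSH's files allow: report applications, acceptances and refusals for the same three groups. The article does not say that refused applications are kept, so this should not be a condition.

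The cost of items 1 to 3 is an edited sentence, two more table rows and two more covariates in a model with about 1,000 children (288 in the Liljeborg-only analysis). Both measures are already planned for all children at baseline, before the maintenance intervention begins, so no further contact with families is needed. They will not capture every trait on which intake could act, so the general caveat about selection bias should stay.

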### Perspectives

It is an ongoing challenge to maintain effects of public health interventions in the long-term e.g., positive changes in life satisfaction or weight loss. Additionally, long-term effects of interventions are often not measured nor reported. This quasi-experimental study will provide new knowledge on the potentials and effectiveness of individualized maintenance interventions on long-term effects on life satisfaction and weight loss among children. The qualitative process evaluation will provide knowledge on what kind of support families need to be able to help their child maintain a healthier lifestyle and the physical, mental, and social health benefits from the health camp as they return to their home environment.

Practicians and researchers call for practice-based research in order to produce findings which are relevant to practicians and may refine and improve current practice (49). It is however challenging to evaluate real world practice in a research design. Real world practice is often developed and implemented based on tacit assumptions, experiential knowledge, ‘practice wisdom'(50) and rules of thumb rather than theory, evidence, and by use of systematic planning tools. We present a systematic approach to evaluate real world practice in a strong research design along with the related challenges and potentials. This may inspire other researchers who are commissioned to evaluate real world practice.

Levels of implementation and fidelity are positively associated with intervention effects (51, 52). It is however challenging to assess the implementation level in individualized, tailored, dynamic interventions such as the extended maintenance intervention where the exact content, dosage and length of the intervention for each child and family is based on the “clinical” judgement of the intervention provider. Our study will propose new approaches to assess the fidelity and the level of implementation in such interventions inspired by goal attainment scaling (38).

## Ethics and Dissemination

### Ethical Issues

In spite of good intentions, public health interventions may have unintended consequences at both the organizational and individual level (53). We will explore potential unintended consequences of the extended maintenance interventions as part of the qualitative and quantitative studies. The extended maintenance intervention is presumed to have a positive effect on body satisfaction as the children become healthier, lose weight, and get higher self-esteem. However, the focus on health and weight loss at camp could potentially result in body dissatisfaction (54). We will investigate the direction of this association as part of the effect analyses on explorative outcomes.

Another ethical challenge is the fact, that we have been informed that the evaluation will have implications for the future of the extended maintenance intervention. If the evaluation does not show an effect it is uncertain if and in what form the intervention will continue and therefore also whether the intervention coordinators can keep their jobs. Thus, our presence as evaluators might put them in an uncomfortable situation where they feel like they are being judged on their job abilities. We will pay attention to this especially during our observations and interviews and highlight that the aim of the qualitative study is to understand the perspectives of the intervention of the participants and providers, the working mechanisms of the intervention along with facilitators and barriers for implementation. Our task is not to evaluate whether they are doing their job sufficiently. Furthermore, we will not evaluate the effectiveness of the intervention based on the qualitative study. The effect study is based on child questionnaires. To address some of these uncertainties, it is important for us as evaluator to have a good understanding of the intervention confer the workshops on program theory and barriers and facilitators and to talk openly with the intervention coordinators about any concerns they might have concerning the evaluation study. Furthermore, we will pay attention to not exposing any of the intervention coordinators in the dissemination of the qualitative findings.

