#### Eligibility Criteria and Recruitment

##### Inclusion

All 7–14-year-olds who are signed up for a 10-week stay at one of the five health camps in the period from September 2019 to June 2021 will be enrolled in the effect evaluation. This also includes children who do not complete the health camp, according to the principle of intention to treat.

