School satisfaction	*Are you happy about your school?*	DCSH	All children	– Baseline – Post health camp – Short-term follow up – Long-term follow up	5 (Yes, always) to 0 (No, never)
	*Do you feel part of the community in your class?*	The Well-being Despite Study(54)	All children	– Baseline – Post health camp – Short-term follow up – Long-term follow up	4 (there is no community in my class) to 0 (always)
	*Most students in my class(es) are kind and helpful*	HBSC	Children 10–14 years	– Baseline – Post health camp – Short-term follow up – Long-term follow up	4 (strongly agree) to 0 (strongly disagree)
	*Other students accept me as I am*	HBSC	Children 10–14 years	– Baseline – Post health camp – Short-term follow up – Long-term follow up	4 (strongly agree) to 0 (strongly disagree)
Body satisfaction	*Are you satisfied with your body?*	Danish Youth Profile(43)	All children	– Baseline – Post health camp – Short-term follow up – Long-term follow up	9 (10 very satisfied) to 0 (1 very dissatisfied)
Parental health promoting behavior	*State how often your family* • *Eat candy, chips, ice cream, cake, or chocolate* • *Eat fast food (e.g. Pizza, kebab, shawarma, burgers, or sausages)* • *Eat fruit* • *Eat vegetables* • *Are observant of portion size* • *Drink coke or soda with sugar*	Modified from HBSC and DCSH	Parents	– Baseline – Post health camp – Short-term follow up – Long-term follow up	6 (never) to 0 (every day, more than once)
	*State how often your family* • *Eat foods marked with whole-grain symbol* • *Eat food with ‘healthier choice' symbol*	Modified from HBSC and DCSH	Parents	– Baseline – Post health camp – Short-term follow up – Long-term follow up	7 (never) to 0 (do not know the symbol)
	*State how often your family* • *Eat breakfast together* • *Eat dinner together*	Modified from HBSC and DCSH	Parents	– Baseline – Post health camp – Short-term follow up – Long-term follow up	5 (never) to 0 (every day)
	*How often do you usually exercise in your free time so much that you get out of breath or sweat?*	Modified from HBSC	Parents	– Baseline – Post health camp – Short-term follow up – Long-term follow up	5 (every day) to 5 (rarely or never)
	*How often does your partner usually exercise in his or her free time so much that he or she get out of breath or sweat?*	Developed for study	Parents	– Baseline – Post health camp – Short-term follow up – Long-term follow up	6 (every day) to 0 (I do not have a partner)

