### Sample Size Calculations

In total 1,038 children will attend the 10-week stay at one of the five camps during the recruitment period (see Figure 4). Approximately 288 will attend Liljeborg health camp and half (~144) will receive the extended maintenance intervention and the other half (~144) the standard maintenance intervention. The 750 children from the four other residential health camps are offered a standard maintenance intervention as well. We know from records at the health camps, that approximately 8% do not complete their stay at the camps. We do, however, have no knowledge of how many children turn down the offer of standard or extended maintenance.

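### The planned check on body dissatisfaction can test extended maintenance but not the camp, and it is assigned to an outcome class that does not contain the item

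*Protocol article*

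**What the plan says.** All places are in the protocol article.

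- **Ethical Issues** first says that unintended consequences of the extended intervention will be explored in both the qualitative and the quantitative studies, and presumes that this intervention improves body satisfaction. It then raises the opposite possibility and locates it in the camp: "the focus on health and weight loss at camp could potentially result in body dissatisfaction". The next sentence assigns the check: "We will investigate the direction of this association as part of the effect analyses on explorative outcomes".
- **Data Analysis** defines the effect analyses: "We will analyze the effectiveness of the extended maintenance intervention compared to control group 1 on the primary and secondary outcomes", by linear regression, and "on explorative outcomes using logistic regression analyses". Graphs over time are planned for the primary and secondary outcomes only. A sensitivity analysis is restricted to the Liljeborg camp.
- **Inclusion** enrols children "who are signed up for a 10-week stay at one of the five health camps", and **Sample Size Calculations** states: "In total 1,038 children will attend the 10-week stay at one of the five camps during the recruitment period". No group goes without camp.
- **Table 3** lists one body satisfaction item, "Are you satisfied with your body", scored 0 to 9 and asked of all children at baseline, post camp, 3 months and 1 year. It stands under intermediate outcomes, as it does in the research questions of the Introduction. The explorative block holds parent-reported life satisfaction, WHO-5 and the symptom checklist.

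**The concern.** The possible harm is tied to the camp, but the analysis named for it compares two groups that both took the camp. An effect shared by both groups drops out of such a comparison, whatever its size. The sentence also sends the item to the explorative class, where Table 3 does not list it, and Data Analysis names no model for the class where Table 3 does list it.

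This is the one harm to the children that the article links to a measured outcome. Without clearer wording, a reader of the results could take a null group difference on body satisfaction as information about the camp's weight focus, which it would not be.

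**Working it through.** **1. The plan's own figure.** The only computed design figure is the detectable difference on the Cantril ladder. The point does not depend on it, but it fixes the group sizes. With SD 2.1, 80% power and two-sided 5% (alpha is not stated, so this is an assumption), the detectable difference is (1.96 + 0.842) × 2.1 × √(1/n₁ + 1/n₂).

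- 144 versus 894: 0.528 (stated 0.53).
- 132 versus 822: 0.552 (stated 0.55).

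Both reproduce.

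**2. What the group comparison estimates.** Let d be the added effect of extended maintenance, and let c_E and c_S be the mean camp effects in the extended and standard groups. The comparison estimates d + (c_E − c_S). If c_E = c_S, the camp effect disappears and only d is left. The same holds for the logistic model stated for explorative outcomes: with d = 0 and equal camp effects, and groups otherwise alike, both groups have the same outcome distribution, so the odds ratio is 1 at any cut-point.

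**3. Simulation.** 144 versus 894 children, baseline-adjusted linear regression (standing in for the logistic model), 4,000 runs, d = 0. Assumed: SD 2.1 and pre-post correlation 0.5.

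| Common camp shift | Group difference | Rejection, group test | Mean within-child change | Rejection, change |
|---|---|---|---|---|
| 0 | -0.002 | 5.0% | 0.00 | 5.2% |
| -0.5 | 0.003 | 4.8% | -0.50 | 100% |
| -1 | -0.002 | 5.1% | -1.00 | 100% |
| -2 | 0.001 | 5.2% | -2.00 | 100% |

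The group test rejects only at its type I error rate. The within-child change recovers the shift because the simulation contains no other source of change; real data would.

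**4. How far exact cancellation can be relied on.**

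- *Camps may differ.* Of the 894 controls, 750 attend the four other camps and 144 attend Liljeborg. With camp effects c_L at Liljeborg and c_O elsewhere, the comparison picks up c_L − (144/894 × c_L + 750/894 × c_O) = 0.84 × (c_L − c_O). That is a difference between camps, not the effect of camp. In the Liljeborg-only analysis this term is zero.
- *Not every child completes.* The article says "approximately 8% do not complete their stay at the camps", for the camps together. Equal non-completion leaks nothing. If completion differed by an assumed 2 to 5 percentage points, a 1-point camp shift would leak 0.02 to 0.05 points into the group difference.

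**5. Other planned analyses.** The dose analysis concerns maintenance. The graphs leave body satisfaction out. The qualitative observations cover eight families, all in the intervention group.

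**6. Precision of a before-after description.** Completers: 1,038 × 0.92 = 955, with response expected to be close to 100% at baseline and post camp (Child Questionnaires). The 95% half-width is 1.96 × SD/√955, with the SD of change assumed:

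- SD 2.0: 0.13 points.
- SD 2.5: 0.16 points.
- SD 3.0: 0.19 points.

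**The case against.** The strongest reply is that the sentence promises something else. The paragraph opens with unintended consequences of the extended intervention, and the relationship to which it first gives a direction is that intervention's effect on body satisfaction. The program theory section says that the extended intervention, like the camp, attends to weight-related behaviour. On this reading the group comparison is the right tool. This stands as a fair reading. A reader might infer that the article plainly commits to testing camp-caused harm with an analysis that cannot do it; the wording is too loose to support that. But on the milder reading, the harm located at camp in the sentence before has no specified analysis.

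Other parts of the reply also stand:

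- The expected difference is exactly zero only if camp effects are equal across camps, and the article does not document that.
- It would be wrong to object that group means hide children who get worse. Logistic regression is stated for explorative outcomes and compares proportions, and subgroup analyses are planned.
- Nothing in the article says that a null difference will be presented as reassurance about the camp.
- The article promises qualitative as well as quantitative exploration, so the group comparison is not the only planned look at unintended consequences.
- A before-after change has no no-camp comparator and cannot settle causation.

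It may also be said that descriptive summaries belong in a fuller plan. That excuses their absence here. It does not excuse pointing to a comparison that cannot address the camp, or the conflict of outcome class, both of which are in the article's text.

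**Conclusion.** The point holds in limited form. The analysis named in Ethical Issues can estimate the added effect of extended maintenance on body satisfaction. It cannot estimate a camp effect common to both groups, whatever its size, because no group goes without camp. If camps differ, the comparison carries 0.84 of the difference between Liljeborg and the other camps, which still does not measure the camp effect. Whichever way the ambiguous sentence is read, the harm located at camp has no analysis specified that could show it. The class conflict, explorative in one section and intermediate in two others with no model named, is a plain inconsistency.

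A reader might infer that the study is blind to worsening body image, or that a before-after analysis would prove or exclude harm from the camp. Neither follows: the item is collected at four time points, and the change in it is uncontrolled. No primary or secondary estimate is affected, so this is a low-cost improvement. The simulation rests on the assumed SD and correlation and on a linear model; the cancellation argument itself rests on none of these.

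**What to change.** 1. In Ethical Issues, state that the extended-versus-standard comparison of body satisfaction, adjusted for the child's own baseline score, addresses the maintenance intervention only, and that a null result says nothing about the camp.
2. Add a descriptive within-child change in body satisfaction from baseline to post camp in all children at the five camps, with the proportion whose score falls. Follow it to 3 months and 1 year by group.
3. Label this change as uncontrolled. It is open to regression to the mean and to the post-camp answer being given on the last day at camp, and at later time points it is mixed with maintenance effects. It can signal worsening; it cannot prove or exclude harm caused by the camp. On a single item some scores will fall by chance alone, so the proportion should be read together with the mean change.
4. Make the outcome class of body satisfaction, and the model used for it, agree across the research questions in the Introduction, Table 3, Data Analysis and Ethical Issues.

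The cost is a little extra descriptive analysis of data already being collected. The limitation that remains is the lack of a no-camp comparator.
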